**Figure 4: Neonatal Study Eligibility Flow Diagram**

[figure not shown]

### Definitions of cases and controls for the data analyses

Cases born  $<38^{+0}$  weeks' gestation for the data analyses will include all births at  $<38^{+0}$  weeks whether or not they present with IUGR/SGA (groups A and C).

IUGR/SGA cases for the data analyses will include the operational definition of IUGR/SGA cases (group B) plus those cases born  $<38^{+0}$  weeks who are also IUGR/SGA (group C); the latter were collected as a sub-set of cases born  $<38^{+0}$  weeks.

Infants in group C (IUGR/SGA infants born  $<38^{+0}$  weeks) will be included in both groups of cases, as the case-control analyses will be carried out separately for each outcome.

The table below provides the definition of controls for the analyses.

Controls for cases born  $<38^{+0}$  weeks will be a sample of live and stillborn infants born  $\geq 38^{+0}$  weeks. In the statistical analyses, a proportion of term IUGR/SGA (xB) cases will be added to the operational controls (group D).

Controls for IUGR/SGA cases will be a sample of live and stillborn infants who are not IUGR/SGA at birth. In the analyses, they will include all operational controls (group D) plus a proportion of infants born  $<38^{+0}$  weeks who are not IUGR/SGA at birth (xA).

Table 2. Case-control comparisons in the data analyses.

| Comparison                                       | Cases | Controls | Comments                                                                                                                                                                                                                                                     |
|--------------------------------------------------|-------|----------|--------------------------------------------------------------------------------------------------------------------------------------------------------------------------------------------------------------------------------------------------------------|
| Infants born $<38^{+0}$ weeks case-control study | A + C | D + xB   | To reproduce the control population, set B (IUGR/SGA only) will be down-weighted by a factor x which is equal to the sampling fraction for set D, that is the proportion of all infants in the control pool who were included in the detailed study (cases). |
| IUGR/SGA case-control study                      | B + C | D + xA   | As above, for set A (infants born $<38^{+0}$ weeks only).                                                                                                                                                                                                    |

Subgroup analyses will include cases born  $<38^{+0}$  weeks, stratified according to: a) gestational age groups (the exact groupings will be decided based on the number of births each week of gestational age, so that there will be at least 100 cases in each sub-group) or b) by preterm phenotype, using the newly proposed INTERGROWTH-21st classification system. For IUGR/SGA, subgroup analyses will include stratification by: a) IUGR/SGA severity ( $<3^{rd}$ , 3-5th, 6th-9th centiles) and b) gestational age.

Appendix II provides more detailed information on different strategies for selecting controls for case-control studies than we considered when planning the study, but some of these proposed strategies were not practical. As proposed above, INTERBIO-21st will adopt a traditional case-non-case design, and odds ratios will be used to estimate relative risks. This is based on the assumption that cases will be relatively rare, i.e.  $<10\%$  of the overall number of births.

We estimate that the overall birth rate for infants born  $<38^{+0}$  weeks will be  $<10\%$  and the overall IUGR/SGA rate will be  $<10\text{--}15\%$ . However, by collecting data on all four sets (A, B, C and D), it will also be possible, with appropriate statistical weights in the analyses, to carry out case-base analyses using Poisson regression with robust variance, if the outcomes end up being more common ( $>10\%$ ).

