Because of the different populations in the centres selected, all analyses in this case-control strategy will be stratified by centre, and will only be pooled if there is no statistical evidence of heterogeneity.

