#### Operational definition of cases and controls in the maternity wards

To simplify the identification of cases and controls during screening, the following procedures will be used (see instructions in Appendix II):

First, gestational age will be assessed using CRL or HC. **Cases, born at  $<38^{+0}$  weeks, will be live or stillborn infants with gestational age assessed by an early ultrasound (either CRL at  $<14$  weeks or HC at  $<24$  weeks)**, regardless of whether or not they presented with IUGR/SGA at any time during pregnancy or at birth. These infants correspond to groups A and C in the table above.

Second, BW for gestational age will be assessed for infants born  $\geq 38^{+0}$  weeks. **Cases, IUGR/SGA, will be live or stillbirths whose BW for gestational age is below the 10th centile of the INTERGROWTH-21st neonatal standard as defined on the form.** These infants correspond to group B in the table above. In the data analysis phase, infants from group C (IUGR/SGA infants born  $<38^{+0}$  weeks) will be added to those in group B so as to include all IUGR/SGA infants regardless of their gestational age at birth.

Third, the screening form will also identify **potential controls, that is, non-IUGR/SGA infants who were not born  $<38^{+0}$  weeks** (group D in the table above). The first potential control born after each case (either a case born  $<38^{+0}$  weeks or an IUGR/SGA case) in the same hospitale will be enrolled in the study as a control. After enrolling a case, a control must be recruited. If two cases are born in succession, the second case cannot be recruited and instead screening for a control continues. Once a case-control pair have been recruited and processed, sites then screen for another case.

At each site, 200 cases born  $<38^{+0}$  weeks and 200 IUGR/SGA cases will be recruited, along with 400 controls. If a site collects 200 cases born  $<38^{+0}$  weeks before it has collected 200 IUGR/SGA cases, it will stop recruiting cases born  $<38^{+0}$  weeks and their corresponding controls, and will continue recruiting IUGR/SGA cases until 200 (and their controls) have been recruited - and vice-versa, if the quota of 200 IUGR/SGA cases is collected before 200 cases born  $<38^{+0}$  weeks are enrolled.

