e If there is more than one hospital at a given study site, and if presumed risk factors vary by hospital (e.g. one primarily attracts mothers of low socioeconomic status, and another attracts high income mothers), it may be necessary to weight the analyses to reproduce a control group that is representative of the study population; ignoring such differences may lead to overmatching.

Note that the only criteria for matching cases and controls are: a) hospital of birth and b) approximate date of birth (usually same day, sometimes the next day if there are no controls on the same day).

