### Study design

For this proof-of-concept study, we will randomly select 500 term IUGR/SGA cases from the INTERBIO-Bank. The 500 normal birth weight controls will be taken either from the population at least risk within the INTERBIO-21st Fetal Study or from the total with normal outcomes from the entire study population, and matched with the cases. A final decision will be made by the INTERBIO-21st Steering Committee.

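### Neonatal Study controls are chosen by hospital and birth date, but the stated analysis stratifies by centre with no date term, so if the two case quotas close at different times the odds ratios can be biased in either direction

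*Protocol*

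**What the plan says.** All references are to Protocol Appendix K.

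**Recruitment.** The section on the operational definition of cases and controls takes as control "The first potential control born after each case" in the same hospital. It adds that "the only criteria for matching cases and controls are: a) hospital of birth and b) approximate date of birth". Each site recruits 200 cases born before 38 weeks, 200 IUGR/SGA cases and 400 controls. If the early-birth quota fills first, the site is told that "it will stop recruiting cases born $<38^{+0}$ weeks and their corresponding controls, and will continue recruiting IUGR/SGA cases until 200" are reached, and the reverse applies if the IUGR/SGA quota fills first.

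**Analysis.** The section on definitions for the data analyses, with its Table 2, sets the comparison groups. For early birth, "In the statistical analyses, a proportion of term IUGR/SGA (xB) cases will be added to the operational controls (group D"). For IUGR/SGA, the controls are all of group D plus a down-weighted part of group A. The same section says "INTERBIO-21 st will adopt a traditional case-non-case design, and odds ratios will be used to estimate relative risks". The text after Box 1 says that "all analyses in this case-control strategy will be stratified by centre, and will only be pooled if there is no statistical evidence of heterogeneity".

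**Hospital.** Footnote e says that weighting to a representative control group may be needed if a site has several hospitals with different risk profiles. It does not mention date.

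**The concern.** Taking the next birth in the same hospital gives each case type a control series with the same hospital and calendar mix. Pooling all of group D for both outcomes removes that balance whenever the two quotas close at different times. The stated stratifier, centre, does not restore it.

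The early-birth and IUGR/SGA rates that the protocol expects are not the same (below 10% and below 10-15%), so equal filling cannot be presumed. The exposures of interest include malaria, other infection and malnutrition, and constancy over time should not be assumed for them. What is at stake is an odds ratio that partly reflects when infants were recruited. Its direction depends on which quota closed first and on whether exposure was rising or falling.

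**Working it through.** **1. The plan's own counts.** 200 + 200 cases at one control each gives 400 controls and 800 pregnancies per site. The overall 2,000 controls and 2,000 cases correspond to 2,000/400 = 5 centres. These figures reproduce.

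**2. A plausible lag.** The protocol gives only upper bounds, so I take them as rates: early birth 10%, IUGR/SGA 10% or 15%. Assumption: 15% of early births are also IUGR/SGA. These count towards the early-birth quota, so the term IUGR/SGA rate is 10 − 0.15×10 = 8.5%, or 15 − 0.15×10 = 13.5%.
- At 8.5%, the early-birth quota fills first, and the IUGR/SGA quota then stands at n = 200×8.5/10 = 170.
- At 13.5%, the order reverses, and the early-birth quota stands at n = 200×10/13.5 = 148.

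**3. Bias in a simple two-period model with no true effect.** Let n be the slower type's count when the faster quota closes. Let p1 and p2 be exposure prevalence before and after closure (assumed).
- Group D has 200 + n controls before and 200 − n after. Control prevalence is k = [(200+n)p1 + (200−n)p2]/400.
- All cases of the faster type fall before closure, so their prevalence is p1.
- The slower type's prevalence is a = [n·p1 + (200−n)p2]/200.
- The odds ratio is the case odds divided by the control odds.

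Worked example, n = 148, p1 = 20%, p2 = 40%: k = (348×0.2 + 52×0.4)/400 = 0.226. The faster type's OR is 0.25/(0.226/0.774) = 0.856. For the slower type, a = (148×0.2 + 52×0.4)/200 = 0.252 and the OR is (0.252/0.748)/(0.226/0.774) = 1.154.

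| n of 200 | p1 to p2 | k | OR, faster type | OR, slower type | False positives, faster type |
|---|---|---|---|---|---|
| 170 | 20% to 30% | 0.2075 | 0.955 | 1.046 | 5% |
| 170 | 20% to 40% | 0.215 | 0.913 | 1.091 | 7% |
| 148 | 20% to 30% | 0.213 | 0.924 | 1.079 | 6% |
| 148 | 20% to 40% | 0.226 | 0.856 | 1.154 | 10-11% |
| 100 | 20% to 30% | 0.225 | 0.861 | 1.148 | 10% |
| 100 | 20% to 40% | 0.250 | 0.750 | 1.286 | 26-27% |

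False-positive rates come from 40,000 simulated datasets per row (5% Wald test of the crude log odds ratio). The rows with n = 100 assume a lag for which the protocol gives no basis. If n = 200 or p1 = p2, every OR is 1.00.

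**4. Adding the xA/xB infants and group C does not remove the bias.** Take early-birth and term IUGR/SGA rates of 10% and 15%, so n = 133.3. Let x = 0.25/0.75 = 1/3, taken as the case rate over the non-case rate. For early birth, the controls before closure are 333.3 + 200/3 = 400 and after closure 66.7, so 14% are late, against 33% of cases. For IUGR/SGA, 4% of cases and 19% of controls are late. With exposure 20% then 30%, null odds ratios become 1.12 (early birth) and 0.92 (IUGR/SGA); with 20% then 40%, 1.23 and 0.85. At rates of 5% and 15% with exposure 20% then 40%, they become 1.43 and 0.74. Conditioning on period returns 1.00 in each case.

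**5. Hospital, for multi-hospital sites only.** Assume two equal hospitals with exposure 10% and 50%.
- Hospital-matched controls, true OR 1.7, hospital ignored: case prevalence is (0.159 + 0.630)/2 = 0.394 and control prevalence 0.30, so the OR is 1.52.
- Controls weighted to all births, no true effect, case rates 5% and 15%: case prevalence is (5×0.10 + 15×0.50)/20 = 0.40 and control prevalence 0.30. The OR is (0.4/0.6)/(0.3/0.7) = 1.56.

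Weighting controls to the population therefore does not adjust for hospital.

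**The case against.** The strongest reply has four parts.

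- **Model terms belong in an analysis plan.** The protocol gives no regression model or covariate list. Its design label is set against case-base sampling and does not say that the odds ratios are crude. The technical note on control selection listed in the Appendix K contents is also not in the text at hand. This stands in part: a later plan may add the terms. However, the protocol itself fixes the control set, the down-weighting and the stratifier, so those statements need the addition.
- **Dropping the pairs is legitimate.** This stands. Consecutive-birth matching is loose, and sharing group D roughly doubles the controls per comparison. A reader might infer that breaking the pairs is itself an error. It is not, provided hospital and period are accounted for.
- **Footnote e foresees the hospital problem.** This stands in part, so it would be wrong to say that the plan considers centre alone. The provision is conditional, though, and its remedy is weighting rather than adjustment. A site with one hospital has only the date issue.
- **The size is speculative.** This stands for large effects. They need a long lag and a marked exposure shift around quota closure, and the documents give neither.

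**Conclusion.** The point holds as a mismatch between matched recruitment and a centre-stratified analysis that uses all of group D with no stated date term. Bias requires two conditions together: the quotas close at different times, and exposure differs between the periods. With lags derived from the protocol's own rate bounds, and exposure assumed to rise from 20% to 30-40%, a null odds ratio for the faster-filling outcome falls to about 0.86-0.95. The slower-filling outcome moves the other way, to about 1.05-1.15. False-positive rates stay between 5% and about 11%. Bias as large as 0.75 needs a lag that the documents do not support.

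A reader might infer that date and hospital differences are bound to enter the odds ratios. The documents do not show that, because both conditions above may fail.

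A reader might also extend the point to Programme II, where controls are matched but Table 1 sizes independent proportions. That is not supported. The control source is left to the Steering Committee and no matching factors are named. The independent-samples calculation is also conservative when pairs are positively correlated: with 500 pairs, 0.2 against 0.3 and alpha 0.0005, power is 57% unmatched and 63% at an assumed pair correlation of 0.1.

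This is a cheap and worthwhile improvement. It does not invalidate the design.

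**What to change.** In the stratification statement after Box 1 and in the section on definitions for the data analyses, state that each case-control comparison is adjusted for or stratified by hospital of birth and calendar period of birth, as well as centre. Hospital-by-month strata or equivalent model terms would do. Individual pairs need not be retained.

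State also that x for the xA and xB infants is calculated within recruitment period, because the sampling fractions change once a quota closes. This makes the change slightly more than a wording edit.

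No new data are needed, since hospital and birth date already drive recruitment. The cost is a small loss of precision: group D controls from periods with no cases of a given type add nothing to that comparison. For the faster-filling outcome, with equal prevalence in cases and controls, the standard error is inflated by √[(1/200 + 1/(200+n))/(1/200 + 1/400)]. That is about 1% at n = 170, 2% at n = 148 and 5% at n = 100.

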**Box 1: Some unique characteristics of studies conducted using NCSS protocols**

Geographically diverse populations

Large, population-based, sample size with severe morbidity and mortality outcomes

Early pregnancy dating by ultrasound provided by small number of standardised operators

Standardised methodology for maternal, newborn and infant follow-up anthropometric measures

Maternal morbidities during pregnancy captured prospectively

Environmental characterisation of the populations and individual participants

However, we recognise the need to enrich the collection of complicated pregnancies from populations with other risk factors that are especially relevant to the needs of developing countries. Therefore, we will supplement sample collection in the three INTERGROWTH-21st centres by also collecting samples from pregnancies from the general population in resource-poor settings where there is a high risk of fetal growth impairment and preterm delivery because of infection, malnutrition, poor socio-economic status and past adverse pregnancy outcomes. This strategy will increase the generation of cases from a relatively small population given the higher incidence of the conditions.

In these centres, we will collect and store samples from 800 pregnancies per centre:

Maternal blood, maternal faeces, cord blood and placental samples will be collected from pregnancies (cases) that have delivered at  $<38^{+0}$  weeks gestation ( $n=200$  per centre) or have resulted in IUGR/SGA newborns ( $n=200$  per centre). Newborns that were born at  $<38^{+0}$  weeks' gestation and were IUGR/SGA will be included in both sets of cases as the case-control analysis will be carried out separately for each outcome.

We will also collect the same samples from term AGA newborns (controls), i.e. non-IUGR, normal birth weight newborns at term, as a reference group ( $n=400$  per centre, i.e. one control for each case).

All cases and controls are required to have had, reported in their medical records, an estimation of gestational age by ultrasound measurement of either CRL  $<14$  weeks or HC  $<24$  weeks. When LMP is available this should also be recorded. If the LMP is not available it should be recorded as such and ultrasound estimations will be used.

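### INTERBIO Neonatal Study: the control weight x assumes every case is enrolled, but the recruitment rules leave some cases out, so x is too small

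*Protocol*

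**What the plan says.** All references are to the Protocol, Appendix K (INTERBIO-21st).

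- **Selection of Cases and Controls, table.** Births fall into four sets: A (<38 weeks, not IUGR/SGA), B (IUGR/SGA, ≥38 weeks), C (both) and D (neither). The table enters A, B and C in full and samples D to the size A + B + C.
- **Definitions of cases and controls for the data analyses, Table 2.** The <38-week comparison sets A + C against D + xB. To rebuild the control population, "set B (IUGR/SGA only) will be down-weighted by a factor x which is equal to the sampling fraction for set D". The IUGR/SGA comparison sets B + C against D + xA, with the note "As above, for set A".
- **Operational definition of cases and controls in the maternity wards.** Each enrolled case must be followed by a control: "If two cases are born in succession, the second case cannot be recruited and instead screening for a control continues". Then, "Once a case-control pair have been recruited and processed, sites then screen for another case". There is also a quota stop. A site that reaches 200 cases born <38 weeks first stops taking them "and will continue recruiting IUGR/SGA cases until 200 (and their controls) have been recruited"; the mirror rule applies where the IUGR/SGA quota fills first.
- **Box 1 and the text after it.** In the resource-poor centres "we will collect and store samples from 800 pregnancies per centre", i.e. 200 + 200 + 400.

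**The concern.** Table 2 treats set B (or A) as fully enrolled and thins it to match the sampling of D. The ward rules mean that B and A are themselves only partly enrolled, so x thins a set that has already been thinned. Term IUGR/SGA infants are then under-represented among the <38-week controls, and non-IUGR/SGA early births among the IUGR/SGA controls.

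The factors under study include HIV, malaria, malnutrition and anaemia, which may plausibly be raised in both outcomes. For such a factor the controls look too little exposed and the odds ratio comes out too high. The error is systematic, so adding sites does not average it away.

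A second effect concerns the cases. Once the quotas close at different times, B and C have different sampling fractions, yet they are pooled unweighted as the IUGR/SGA case group.

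**Working it through.** **Inputs.** The rules are those above, with A and C filling the <38-week quota and B the IUGR/SGA quota. The protocol expects <10% of births at <38 weeks and <10–15% IUGR/SGA. It does not give the overlap C; I assume 2% of births (5% in two high-risk scenarios). Exposure figures are also assumptions: 20% exposed in D, and an exposure odds ratio of 2 or 4 for the under-weighted set against D.

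**1. The plan's own weight under its own premise.** Take A/B/C/D = 8/10/2/80% with every case enrolled.
- f_D = 20/80 = 0.25.
- B's share of D + xB = (0.25 × 10)/(0.25 × 10 + 20) = 2.5/22.5 = 0.111.
- True share = 10/(10 + 80) = 0.111.

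The rule is right if, and only if, all of B is enrolled. The same holds for A.

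**2. Partial enrolment.** To restore B:D, the enrolled B must be weighted by f_D/f_B, and the enrolled A by f_D/f_A. The ratio of x to the right weight is therefore f_B (or f_A).

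**3. Succession rule alone.** Let p be the total case share. A cycle takes 1/p births to find a case and 1/(1−p) to find a control, which is 1/[p(1−p)] births in all. That contains 1/(1−p) cases and 1/p set-D infants, with one of each enrolled. So f_case = 1−p and f_D = p. The right weight is p/(1−p); the stated weight is p.

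| p | stated x | right weight | ratio |
|---|---|---|---|
| 0.15 | 0.15 | 0.176 | 0.85 |
| 0.20 | 0.20 | 0.250 | 0.80 |
| 0.30 | 0.30 | 0.429 | 0.70 |

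**4. Succession rule plus quotas of 200/200** (simulated, 300 replicates per scenario).

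| A/B/C, % | f_A | f_B | x = f_D | right weight, B | right weight, A | C share of B + C: true / enrolled |
|---|---|---|---|---|---|---|
| 8/8/2 | 0.67 | 0.84 | 0.163 | 0.196 | 0.244 | 0.200 / 0.167 |
| 8/10/2 | 0.77 | 0.78 | 0.193 | 0.247 | 0.250 | 0.167 / 0.165 |
| 8/13/2 | 0.80 | 0.61 | 0.206 | 0.338 | 0.259 | 0.132 / 0.166 |
| 8/5/2 | 0.44 | 0.90 | 0.104 | 0.116 | 0.235 | 0.289 / 0.167 |
| 5/13/2 | 0.85 | 0.46 | 0.149 | 0.325 | 0.175 | 0.133 / 0.222 |
| 15/10/5 | 0.39 | 0.78 | 0.222 | 0.285 | 0.574 | 0.335 / 0.202 |
| 10/20/5 | 0.68 | 0.51 | 0.315 | 0.615 | 0.462 | 0.201 / 0.251 |

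A and C share one recruitment stream and have the same fraction, so the A + C case mix is not distorted. The B + C mix is distorted whenever the quotas close at different times.

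**5. Effect on the odds ratio, through the control weights only.** Worked case: 5/13/2, exposure odds ratio 4.
- Exposure is 50% in B and 20% in D. B's share of controls is 0.140 (true) or 0.069 (as weighted).
- True control exposure = 0.20 + 0.30 × 0.140 = 0.242, odds 0.319.
- As weighted = 0.20 + 0.30 × 0.069 = 0.221, odds 0.283.
- Inflation = 0.319/0.283 ≈ 1.13.

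| A/B/C, % | <38-week comparison, exposure OR 2 / 4 | IUGR/SGA comparison, exposure OR 2 / 4 |
|---|---|---|
| 8/8/2 | +1.1% / +2.4% | +2.2% / +4.9% |
| 8/10/2 | +1.8% / +3.8% | +1.6% / +3.4% |
| 8/13/2 | +4.1% / +8.9% | +1.4% / +3.1% |
| 8/5/2 | +0.4% / +1.0% | +3.8% / +8.4% |
| 5/13/2 | +5.7% / +12.6% | +0.7% / +1.5% |
| 15/10/5 | +2.0% / +4.2% | +8.2% / +18.0% |
| 10/20/5 | +7.9% / +16.9% | +3.1% / +6.6% |

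**The case against.** - **Reach is limited.** The growth standards, which are the project's primary objective, do not use x. Nor does the Programme II comparison of 500 term IUGR/SGA cases with 500 normal birth weight controls. This stands.
- **The shift is small beside sampling error at one centre.** Take 200 cases at 40% exposure and about 430 weighted controls at 24%. The standard error of the log odds ratio is √(1/80 + 1/120 + 1/103 + 1/327) ≈ 0.18, so the 95% interval is about ±0.36 on the log scale. This stands for a single centre. Pooled intervals are tighter, while the shift does not shrink.
- **Other text may repair it.** It does not. The footnote on several hospitals concerns differences between hospitals. The statistical weights mentioned later are unspecified and belong to an alternative case-base analysis, used only if outcomes exceed 10%. Stratifying by centre leaves the within-centre error untouched. Subgroups by gestational age would partly reveal the B + C distortion but not correct it.
- **INTERBIO Appendices I and II**, on recruitment and choice of controls, are not in the text at hand and may say more. That limits certainty about how the analysis would be run, but not about what Table 2 states.
- **The counts needed may not exist.** The plan says all infants are screened, but also that sites look for the next case only after a pair is processed, and that the form is completed only where early dating exists. This stands and shapes the fix.

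A reader might infer that all the weighted odds ratios are biased, or that a shift of about 10% is typical. Neither is supported. If exposure is equally common in D and in the under-weighted set, the control weight does no harm. The 10–13% figures need an exposure odds ratio near 4 and quotas that fill at very different times, and the documents give no exposure figures.

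**Conclusion.** Table 2's weight is wrong as written for the Neonatal Study case-control analyses, and it conflicts with the ward rules in the same appendix. The stated aim of rebuilding the control population is right; the formula meets it only under full case enrolment.

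The algebra rests on no assumption beyond the written rules and a stable order of births. Even when both quotas fill together (8/10/2%), x is about 0.19 against 0.25. With unequal quotas it can be less than half the right value (0.149 against 0.325; 0.104 against 0.235).

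The effect on odds ratios is conditional. Near the protocol's rates it is about 0.4–6% at an exposure odds ratio of 2 and 1–13% at 4. At assumed high-risk rates (total case share 30–35%) it is about 2–8% and 4–18%. The direction is upward only for exposures commoner in the under-weighted set than in D. These sizes depend on the assumed overlap and exposure figures.

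**What to change.** 1. In the Selection of Cases and Controls table, replace *(all)* for A, B and C with the number recruited under the ward rules.
2. In Table 2, define the weights as f_D/f_B for set B and f_D/f_A for set A. Each fraction is the number enrolled over all eligible births in that set, at that site, across the whole recruitment period. State the assumption that set proportions and exposure are stable over that period.
3. Add a sensitivity analysis restricted to the period before the first quota closes. Do not use separate weights for each recruitment phase: once a quota closes, f_B (or f_A and f_C) is zero and the weight is undefined.
4. When B and C are pooled as IUGR/SGA cases, weight each by the inverse of its own sampling fraction.
5. Keep the screening form running for every eligible birth, including cases that are not recruited and births while a pair is being processed, and record the date each quota closes.

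The cost is protocol and analysis wording, continued screening counts and a slightly larger variance. Recruitment targets do not change.
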